**IIH:DT Statistical Analysis Plan**  
Property of BCTU University of Birmingham

| Version number | Effective date | Protocol version number | Details of changes (refer to section number of SAP)                                                                                                                                                                                                                                                                                                                                                                                                                                                                                                                                                                                                                                                                                                                                                                                                                                          | Reason for change                                                                                                                                                                                                                                                                                                                                                                                                                                                                                                      | Timing of change with respect to interim/final analysis |
|----------------|----------------|-------------------------|----------------------------------------------------------------------------------------------------------------------------------------------------------------------------------------------------------------------------------------------------------------------------------------------------------------------------------------------------------------------------------------------------------------------------------------------------------------------------------------------------------------------------------------------------------------------------------------------------------------------------------------------------------------------------------------------------------------------------------------------------------------------------------------------------------------------------------------------------------------------------------------------|------------------------------------------------------------------------------------------------------------------------------------------------------------------------------------------------------------------------------------------------------------------------------------------------------------------------------------------------------------------------------------------------------------------------------------------------------------------------------------------------------------------------|---------------------------------------------------------|
| 1.0            | 05/05/17       | 8.0                     | First release                                                                                                                                                                                                                                                                                                                                                                                                                                                                                                                                                                                                                                                                                                                                                                                                                                                                                | -                                                                                                                                                                                                                                                                                                                                                                                                                                                                                                                      | -                                                       |
| 2.0            |                | 8.0                     | 
Minor edits to clinical information in background and units for lumbar puncture (throughout SAP).
Section 6.2: Clarified data to be used from headache diary (headache frequency, severity and duration). Added further information on the assessment of the Fundus photographs by masked neuro-ophthalmologist.
Section 9.12: Added standard definitions for how severity and duration of headache calculated in headache trials. Added how the severity scores from v1 of headache diary will be mapped to scores on v2 of headache diary. Defined worst and best eye.
Section 10.6: Analysis of individual eye will now be based on worse and best eye, rather than left and right eye.
Section 10.6: Analysis of Fundus photograph data clarified.
 
Section 10.10: Analysis now purely descriptive. List of safety data items extended. Data to be analysed
 | 
Clinical clarification. Lumbar puncture unit cmCSF rather than cmH2O.
Missing information from SAP v1.0.
 
Missing information from SAP v1.0.
 
Analysis in line with current practice, and how a recent trial reported their individual eye data
 
Had clarification from the Chief Investigator as to how this data should be analysed, which is also as per a recent trial.
Chief Investigator clarified safety data items they wished to be analysed, and to report means
 | Prior to database lock and final analysis               |

**IIH:DT Statistical Analysis Plan**  
Property of BCTU University of Birmingham

|  |  |  |                                                                                                           |                                                                                       |  |
|--|--|--|-----------------------------------------------------------------------------------------------------------|---------------------------------------------------------------------------------------|--|
|  |  |  | simply as means at each time point,
and proportion above upper or trial
upper limit as appropriate. | and proportion above upper
reference limit or upper trial limit
as appropriate. |  |
|--|--|--|-----------------------------------------------------------------------------------------------------------|---------------------------------------------------------------------------------------|--|

| Abbreviations & Definitions |                                                           |
|-----------------------------|-----------------------------------------------------------|
| Abbreviation / Acronym      | Meaning                                                   |
| AE                          | Adverse Event                                             |
| BCTU                        | Birmingham Clinical Trials Unit                           |
| BMI                         | Body Mass Index                                           |
| DMC                         | Data Monitoring Committee                                 |
| CMO                         | Contract Manufacturing Organisation                       |
| CONSORT                     | Consolidated Standards of Reporting Trials                |
| HIT 6                       | Headache impact test-6                                    |
| ICP                         | Intracranial pressure                                     |
| IIH                         | Idiopathic intracranial hypertension                      |
| ISRCTN                      | International Standard Randomised Controlled Trial Number |
| OCT                         | Optical coherence tomography                              |
| SAE                         | Serious Adverse Event                                     |
| SAP                         | Statistical Analysis Plan                                 |
| TSC                         | Trial Steering Committee                                  |

## **1. Introduction**

This document gives a detailed statistical analysis plan for the IIH:DT trial and should be read in conjunction with the current trial protocol. Any deviations from this plan will be described in the final report or publication (see Appendix A).

## **2. Background and rationale**

The background and rationale for the trial are outlined in detail in the protocol. In brief, IIH:DT is a trial in participants who have idiopathic intracranial hypertension (IIH) which is characterised by elevated intracranial pressure (ICP) and papilloedema. IIH is a condition found almost exclusively in obese women (90%) and causes disabling daily headaches and loss of vision, which is severe and permanent in up to 25% of cases. It is hypothesised that 11 $\beta$ -HSD1 amplifies local cortisol availability at the choroid plexus, thereby increasing cerebrospinal fluid secretion which may increase ICP. Therefore use of an 11 $\beta$ -HSD1 inhibitor may lead to decreasing ICP in IIH.

## **3. Study objectives**

The primary objective is to evaluate whether 12 weeks of treatment with the 11 $\beta$ -HSD1 inhibitor, AZD4017, is a potential treatment for IIH through reduction in ICP.

Secondary objectives are as follows:

- Evaluate the effects of AZD4017 on vision, papilloedema, headache and anthropological measurements (including weight and fat mass distribution) in participants with IIH;
- Evaluate the safety and tolerability of a 12 week course of AZD4017 in participants with IIH.

## **4. Study design**

IIH:DT is a multicentre, prospective, double-blind, placebo-controlled, parallel group, phase II, randomised controlled trial (see Appendix B for trial schema). Participants will be recruited from secondary care from Neuro-ophthalmology or neurology clinics. Participants will be randomised in a 1:1 ratio to either AZD4017 or placebo. Participants will receive either AZD4017 or placebo twice daily for 12 weeks.

## **5. Study comparisons**

All references in this document to 'group' refer to AZD4017 or placebo.

## **6. Outcome measures**

### **6.1. Primary outcome(s)**

The primary outcome is to examine the effect of AZD4017 on ICP, as measured by lumbar puncture in cmCSF, from baseline to 12 week. The primary outcome measure is the difference in ICP at 12 weeks.

## 6.2. Secondary outcomes

Secondary outcomes are as follows:

- IIH symptoms (presence or absence of tinnitus, perceived visual loss, diplopia, visual obscuration and headache) over 12 weeks, and at 16 weeks;
- IIH visual function in both eyes (measured by LogMAR (log of the minimum angle of resolution) chart to assess visual acuity, automated perimetry (Humphrey 24-2 central threshold) to measure the visual field mean deviation and MARs charts to evaluate contrast sensitivity) between baseline, week 12 and week 16;
- Papilloedema evaluated using 1). spectral domain optical coherence tomography and 2). Fundus photographs with Frisen classification (by masked neuro-ophthalmologists to grade the images and who also assess whether the image is better, worse or the same as the image taken at baseline) between baseline, week 12 and week 16;
- Headache associated disability using the headache impact test-6 score (HIT 6), headache diary (to assess headache frequency (days/week), severity and duration) and use of analgesia (days/week) between baseline and 12 weeks, with further analysis between weeks 12 and 16;
- Anthropological measures (e.g. blood pressure, body mass index (BMI), waist/hip ratio and fat distribution);
- Safety and tolerability of AZD4017 measured using adverse event (AE) and serious adverse event (SAE) reporting and safety bloods.

Fundus photographs will be reviewed by three masked neuro-ophthalmologists who will grade the images as described above. The overall grading of an image will be where the majority of the neuro-ophthalmologists are in agreement on a grade, or in the instance where the neuro-ophthalmologists are in disagreement by at most one grade, the median will be taken as the grade. If the neuro-ophthalmologists disagree by more than one grade, these images will be checked by a 4th neuro-ophthalmologist to obtain a consensus grade.

The HIT 6 is a patient completed questionnaire where a score of 36=best outcome, and a score of 78=worst outcome.

The Headache Diary is completed over 7 days at baseline (participants complete daily headache diary in week before screening visit) and weeks 12 and 16 (participants complete daily headache diary in week prior to visit). Severity (0-5)\* and duration (over each 24 hour period) of headache are reported for each day, along with use of painkillers.

Secondary outcomes will be assessed at weeks 12 and 16 (see Appendix C for a table of assessment times). The safety bloods are also collected at the week 1, week 4 and week 8 time points.

Adverse events and SAEs are collected as and when they occur over the course of the 16 week

follow up.

\*updated version of the headache diary scores severity 0-10 (see section 9.12).

## 7. Randomisation

Randomisation will be performed by the Contracting Manufacturing Organisation (CMO), Almac, who are supplying and coding the study medications on behalf of AstraZeneca. Block randomisation will be used so that each block of trial numbers contains a random assignment of equal numbers of active and placebo treatment allocations. Participants will be randomised in a 1:1 ratio to receive either AZD4017 or placebo.

Tablets containing either AZD4017 or matching placebo will be prepared by Almac appointed by AstraZeneca.

## 8. Sample size

A total of 30 participants will be recruited, 15 participants in each group (AZD4017 vs. placebo).

To detect a difference between the groups of 14% in ICP (assuming a standard deviation of 10% for ICP) with 90% power and two-sided  $\alpha=0.05$ , requires 12 participants per group. Allowing for 20% drop out, 15 participants are required per group, so 30 participants in total.

## 9. General statistical considerations

### 9.1. Analysis populations

All primary analyses (primary and secondary outcomes) will be by intention-to-treat. Patients will be analysed in the treatment group to which they were randomised, and all patients shall be included whether or not they received the allocated treatment. This is to avoid any potential bias in the analysis.

The safety analysis set will include all subjects who received at least 1 dose of randomised study medication and for whom any post-dose data are available.

A 'per protocol' analysis (defined in section 9.2) for the primary outcome will also be carried out but only as a sensitivity analysis.

## 9.2. Definition of compliance

Compliance to treatment allocation will be monitored by counting the number of tablets that the participant has taken over the 12 week treatment period. Patients are randomised to receive 2x200mg of either AZD4017 or placebo twice daily for 12 weeks. Doses will be taken 12 hours apart, though this will not be monitored. The total number of tablets that a participant should have taken over the 12 week treatment period is 336 tablets. We will define treatment compliance as patients who took at least 80% of the total number of tablets (i.e. 268 tablets). For the per protocol analysis only those patients who took at least 80% of the tablets will be included in the analysis. Missed doses will be documented using both reported missed doses and tablet count (if available).

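### SAP section 9.2 prints 268 tablets as the count for at least 80% of 336, but 268 is 79.76% and fails that rule; the smallest count that meets it is 269

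*SAP*

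**What the plan says.** Section 9.2 gives the regimen as it enters the tablet count: "Patients are randomised to receive 2x200mg of either AZD4017 or placebo twice daily for 12 weeks". It derives the denominator from this: "The total number of tablets that a participant should have taken over the 12 week treatment period is 336 tablets". It then defines compliance by a percentage, with a count in brackets: "We will define treatment compliance as patients who took at least 80% of the total number of tablets (i.e. 268 tablets". The next sentence sets the analysis population and gives only the percentage: "For the per protocol analysis only those patients who took at least 80% of the tablets will be included in the analysis".

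The definition is used in two places. Section 10.3 cross-tabulates allocated treatment by the compliance categories of section 9.2. Section 10.8 lists a per-protocol analysis in the population described in section 9.2; section 9.1 says that this analysis "for the primary outcome will also be carried out but only as a sensitivity analysis".

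**The concern.** The bracketed count is introduced as another way of stating the percentage, so the two should select the same participants. They do not, because an at-least rule on whole tablets needs the product rounded up, and 268 is the product rounded down.

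One programmer may code the condition as 268 tablets or more, and another as 80% of 336 or more. Each can point to section 9.2, and the section does not say which governs. A participant at exactly 268 would be compliant in one program and non-compliant in the other. It is best to settle this before anyone has seen results by arm, so that no choice of reading is left for later.

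**Working it through.** **Inputs, all from SAP section 9.2 unless stated**

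- Tablets per dose: 2. Doses per day: 2.
- Treatment period: 12 weeks = 12 × 7 = 84 days.
- Printed total: 336 tablets.
- Rule: at least 80%. Printed count: 268 tablets.
- Section 8: 15 participants per group planned, 12 per group before the 20% drop-out allowance.

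**Step 1. Reproduce the total.** 2 × 2 × 84 = 336. This agrees with the SAP.

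**Step 2. Apply the percentage.** 0.80 × 336 = 268.8. The smallest whole number of tablets k with k/336 ≥ 0.80 is 268.8 rounded up, which is 269.

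**Step 3. Test the two neighbouring counts.**

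| Tablets taken | Share of 336 | Meets at least 80%? | Meets 268 or more? |
|---|---|---|---|
| 267 | 79.46% | no | no |
| 268 | 79.76% | no | yes |
| 269 | 80.06% | yes | yes |

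**Step 4. Look for another origin of 268.** Rounding 268.8 to the nearest whole number gives 269, and so does rounding up. Only truncation gives 268. A treatment period one day shorter or longer does not explain it: 83 days gives 332 tablets and 0.80 × 332 = 265.6; 85 days gives 340 tablets and 0.80 × 340 = 272.0.

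**Step 5. Count the disagreements.** Over every count from 0 to 336, the conditions of 268 or more and 80% or more give different answers at one value only, 268.

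**Step 6. Can that value occur?** Yes. 268 = 4 × 67, which is 67 full days out of 84, or 134 complete doses out of 168. This shows that the value is attainable, not that any participant will have it.

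**Step 7. Size if it did occur.** One participant would be 1/15 = 6.7% of an arm as planned, or 1/12 = 8.3% of an arm of 12. Both figures are conditional on someone having exactly 268 tablets. The SAP does not state a size for the per-protocol set, so the 12 is an assumption borrowed from the sample-size calculation.

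**The case against.** The natural reading of section 9.2 is a single rule, at least 80%, with a carelessly rounded illustration beside it. The percentage appears in both sentences and the count in only one. A careful programmer would probably code the percentage, and the slip would then have no effect.

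The measure is also coarser than the discrepancy. Section 9.2 relies on reported missed doses and on tablet counts where these are available. One tablet is 1/336 = 0.3% of the total, probably within the error of such records.

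Both arguments stand as reasons to grade this as minor. They do not make the printed number right. However imprecise the data, a cut-off has to sort the recorded values in one way, and the definition as printed sorts 268 in two.

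A reader might infer that the per-protocol population is itself defined by a cut-off of 268. The document does not support that, since the sentence that defines this population gives only the percentage. A reader might also take 8% of an arm as the expected effect. That figure applies only if a participant falls on one particular count, and nothing in the SAP suggests that anyone did or will.

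**Conclusion.** The printed count is wrong as written: 268 of 336 is 79.76% and does not meet the SAP's own criterion, while 269 does. Nothing elsewhere in the SAP corrects it.

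The reach is narrow. Only a participant with exactly 268 recorded tablets would be classified differently, and only in one descriptive table and one sensitivity analysis. Under section 9.1 the primary analyses of primary and secondary outcomes are by intention-to-treat, so tablet counts do not enter them. The sample size and power in section 8 do not depend on the compliance definition.

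The conclusion takes the total of 336 and the 80% criterion as the SAP states them. If the total were changed, the count would have to be recalculated.

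**What to change.** Make one of two edits in section 9.2:

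- replace 268 with 269, so that count and percentage agree; or
- delete the count and state that at least 80% of 336 tablets governs both the compliance table in section 10.3 and the per-protocol set in section 10.8.

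The second is slightly safer, because it leaves one rule and no derived number to keep in step with it. Either edit keeps the 80% criterion and changes no analysis method. The cost is one line in the SAP, with an entry in its version history, and a check that the analysis code uses the same condition.

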## 9.3 Handling of protocol deviations and violations

We will apply a strict definition of the intention-to-treat-principle and will consider all randomised patients in the analysis in some form regardless of deviation from the protocol. This includes patients who were randomised but later found to violate the inclusion or exclusion criteria. It does not include those participants who have specifically requested to withdraw the use of their follow-up data in the first instance; however these outcomes will be explored as per other missing responses.

Data collected outside the scheduled window frame (+/- 1 weeks) for all assessment points will be included in the intention to treat analysis, but a sensitivity analysis will also be performed where those patients who returned the forms outside of the assessment window are excluded (see section 10.8 for more details on sensitivity analyses).

## 9.4. Levels of confidence and p-values

Unless otherwise specified, estimates of differences between groups will be presented with 95%, two-sided confidence intervals. P-values will be reported from two-sided tests at the 5% significance level.

## 9.5. Adjustments for multiplicity

No correction for multiple testing will be made.

## 9.6. Interim analysis and stopping rules

If AZD4017 is overwhelmingly better or worse than placebo with respect to ICP, then this effect may become apparent before the target recruitment has been reached. Alternatively, new evidence could emerge from other sources to suggest that AZD4017 is definitely more, or less, effective than placebo. To protect against any unnecessary continuance of the trial in this event, interim analyses of major endpoints and safety data will be supplied during the period of recruitment to the study, in strict confidence, to the Data Monitoring Committee (DMC) along with updates on results of other related studies, and any other analyses that the DMC may request.

The DMC will advise the chair of the Trial Steering Committee (TSC) if, in their view, any of the randomised comparisons in the trial have provided both: a) proof beyond reasonable doubt that for

all, or for some, types of participant one particular intervention is definitely indicated or definitely contra-indicated in terms of a net difference of a major endpoint, and b) evidence that might reasonably be expected to influence the patient management of many clinicians who are already aware of the other main trial results. Unless this happens, however, the TSC, the collaborators and all of the central Trial staff (except the statisticians who supply the confidential analyses) will remain ignorant of the interim results.

Appropriate criteria of proof beyond reasonable doubt cannot be specified precisely, but a difference of at least  $p < 0.001$  (similar to a Haybittle-Peto stopping boundary) in an interim analysis of a major endpoint may be required to justify halting, or modifying, the study prematurely. If this criterion were to be adopted, it would have the practical advantage that the exact number of interim analyses would be of little importance, so no fixed schedule is proposed. Given the proposed use of the Haybittle-Peto boundary no adjustment for multiple testing (to control the overall type I error rate) is proposed, i.e. the threshold for statistical significance at final analysis will still be  $p = 0.05$ .

A separate DMC reporting template will be drafted and agreed by the DMC including an agreement on which outcomes will be reported at interim analyses. The statistical methods stated in this Statistical Analysis Plan will be followed for the agreed outcomes.

